#### EOI assessment

2.6.5

Participants will undergo repeat cognitive assessments and all questionnaires (except for the EHI) as per the baseline assessment. Participants will have a 3 T MRI scan with an identical protocol to the baseline MRI. Participants will be asked to complete an in-house questionnaire exploring the experience and tolerability of the iTBS protocol and MRI scan.

#### 8-Week follow-up

2.6.6

At 8-week follow-up, participants will complete again the cognitive assessments and questionnaires (except for the EHI), followed by a semi-structured interview exploring the acceptability and tolerability of the intervention and any self-reported changes in cognitive ability experienced in daily life. The interview will also explore participants’ views on what a sufficiently meaningful and durable change in cognitive performance is to balance and justify the demands of the intervention (i.e., daily hospital visits, possible discomfort, etc.) Participants will be asked for suggestions for improving the trial experience.

#### Early withdrawal interviews

2.6.7

As this is a feasibility trial, participants withdrawing from the study before completing the protocol will be invited for an exit interview to explore the reasons for withdrawal.

### Endpoints measured

2.7

As this is a feasibility study several endpoints will be collected to allow primary and secondary aims to be assessed, shown in Table 1.

**Table 1 j_med-2023-0814_tab_001:** Feasibility trial endpoints

Endpoints to address the primary objective
Proportion of screened potential participants eligible for participation
Proportion of eligible potential participants consenting for participation
Number of participants completing the visit schedule as per protocol
Questionnaire ratings of tolerability of the iTBS or sham administration
Questionnaire ratings of overall acceptability of trial participation
Number and type of adverse events
Participant opinion at EOT of whether they received real or sham iTBS
**Endpoints to address the secondary objectives**
Scores and test sub-scores in the Brief International Cognitive Assessment for Multiple Sclerosis (BICAMS) test battery
Self-reported cognitive dysfunction: Perceived Deficits Questionnaire (PDQ)
Self-rated mood: Patient Health Questionnaire – Depression (PHQ-9) and Generalised Anxiety Disorder 7 (GAD-7)
Self-reported fatigue: Modified Fatigue Impact Scale (MFIS)
Subjective perceived differences in cognitive abilities in daily life (explored at interview)
Reflections on meaningful changes to cognition in relation to the demands of the trial participation (explored at interview)
Change in effective connectivity between left DLPFC and left caudate nucleus

### Sample size

2.8

We aim to randomise up to 40 participants (up to 10 participants per group), which should provide sufficient information to inform our feasibility objectives and to inform the design of a potential phase III RCT. Whitehead et al. [45] recommend that pilot trial sample sizes should be between 10 and 20 participants per intervention group, to offer 80% power and two-tailed 5% significance level for standardised effect sizes of small (0.2) or medium (0.5). Therefore, with our acknowledgement that the study procedures may be taxing for people with MS, we have selected the smaller target of 10 participants per group to minimize inconveniences for a wider sample, with respect to our primary objective.

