**Figure 1 j_med-2023-0814_fig_001:**
[figure not shown]
Trial flowchart.

Consenting procedures will be conducted by the research psychologist. Participants will be randomised after completing the consent form, and the research psychologist will be blinded to group allocation. Participants will be randomised to one of four groups in equal proportions (1:1:1:1 ratio) automatically using blocked stratified randomisation, stratified on: age group (≤40), gender (man or woman), and MS type (relapsing-remitting MS or secondary progressive or primary progressive MS). The randomisation schema was created on 9th November 2021 10:51 using *ralloc.ado* version 3.5.2 [27] in Stata version 17. The neuromodulation research fellow is notified of the group allocation via an automatic email. The research psychologist and principal investigator will remain blinded to group allocation. The two TMS operators (including the neuromodulation research fellow) administering the iTBS will not be blind to group allocation.

Participants will be blinded as to whether their iTBS intervention is real (groups 1, 2, and 3) or sham (group 4) until the end of their study participation. Although only the 2-week intervention duration has a sham comparator (group 2 = real iTBS, group 4 = sham iTBS), participants will not be made aware that the 1- and 4-week intervention durations do not have a sham comparator. Participants will be instructed not to tell the research psychologist the duration of their intervention, as this would reveal to the research psychologist that the patient received the real iTBS intervention if in the 1- or 4-week intervention groups. To standardise the assessment interval and maintain the blinded status of the research psychologist, the interval between baseline and EOI assessments will be fixed at 5 weeks, requiring commencement of the iTBS intervention to be staggered per group as per Figure 2.

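### The sample-size section attaches 80% power for effects of 0.2 or 0.5 to pilot groups of 10 to 20; unadjusted comparisons with 10 per group have about 7% and 18.5%

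*Protocol article*

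**What the plan says.** Section 2.8 (Sample size) of the protocol article opens with the target: "We aim to randomise up to 40 participants (up to 10 participants per group"), described as enough for the feasibility objectives and for designing a possible phase III trial. It then cites a methodological source said to "recommend that pilot trial sample sizes should be between 10 and 20 participants per intervention group", and gives the purpose of that range as "to offer 80% power and two-tailed 5% significance level for standardised effect sizes of small (0.2) or medium (0.5"). The next sentence begins with 'Therefore', notes that the procedures may be taxing for people with MS, and concludes that "we have selected the smaller target of 10 participants per group", with reference to the primary objective.

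Three other sections bear on this. Section 2.4 allocates the four groups 1:1:1:1. Section 2.2.1 makes feasibility the primary objective. Section 2.9 (Data analysis plan) intends to estimate effect sizes and compare groups on cognition, mood and fatigue, to inform the sample size of a later phase III trial.

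**The concern.** In the sentence as printed, the thing that offers 80% power is the pilot sample size. Nothing assigns the figure to a later trial. Because the next sentence starts with 'Therefore', the power statement becomes part of the reasoning for this trial's 10 per group.

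Groups of 10 to 20 are far too small for 80% power at 0.2 or 0.5 SD in an ordinary two-group comparison. Section 2.9 does plan between-group comparisons, so the misstatement has somewhere to do harm. Someone who takes section 2.8 at face value could treat an inconclusive active-versus-sham difference as coming from a well-powered comparison, and carry that into the phase III planning.

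**Working it through.** **Inputs, all from section 2.8 unless noted:** n = 10 per group (recommended range 10 to 20); two-sided alpha 0.05; claimed power 80%; standardised differences d = 0.2 and 0.5, so SD = 1. Equal allocation is from section 2.4.

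**Step 1: try to reproduce the 80%.** For a two-sample t-test with n per group, the degrees of freedom are 2n − 2 and the non-centrality parameter is d·√(n/2). Power is the probability that the non-central t statistic falls beyond ±t(0.975, 2n − 2).

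| n per group | d | Non-centrality | Power (two-sided 5%) |
|---|---|---|---|
| 10 | 0.2 | 0.2·√5 = 0.447 | 7.1% |
| 10 | 0.5 | 0.5·√5 = 1.118 | 18.5% |
| 20 | 0.2 | 0.2·√10 = 0.632 | 9.5% |
| 20 | 0.5 | 0.5·√10 = 1.581 | 33.8% |

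The normal approximation at n = 10 gives similar values, 6.5% and 20.0%. The stated 80% is not reproduced.

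**Step 2: try other analyses that might have been meant.**

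| Analysis | d = 0.2 | d = 0.5 |
|---|---|---|
| One-sided 5%, 10 per group | 11.2% | 28.5% |
| One-sided 5%, 20 per group | 15.3% | 46.3% |
| Paired test within one group, n = 10 | 8.8% | 29.3% |
| Paired test within one group, n = 20 | 13.6% | 56.5% |
| 30 active versus 10 sham | 8.3% | 26.6% |

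A four-group ANOVA with 40 participants has 7.2% power at f = 0.1 and 21.2% at f = 0.25.

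For baseline adjustment, d is replaced by d/√(1 − r²), where r is the correlation between baseline and outcome. The article gives no r, so 0.5 to 0.9 is assumed. With 10 per group, power runs from 7.8% to 16.3% at d = 0.2 and from 23.1% to 68.0% at d = 0.5. At the top of that range, 0.5/√(1 − 0.81) = 1.147. None of these reaches 80%.

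**Step 3: what 80% power would need.** By the normal approximation, n per group = 2·(1.96 + 0.8416)²/d² = 15.70/d².
- d = 0.2: 15.70/0.04 = 392.4, so 393 per group (394 with the t distribution).
- d = 0.5: 15.70/0.25 = 62.8, so 63 per group (64 with the t distribution).

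Turned round, the difference detectable with 80% power at 10 per group is (1.96 + 0.8416)·√(2/10) = 1.25 by the normal approximation and 1.32 with the t distribution. At 20 per group it is 0.91 with the t distribution.

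**Step 4: what the planned size does deliver.** 95% confidence interval half-widths:
- Proportion near 50% in one group: 1.96·√(0.25/10) = 0.31, about ±31 percentage points.
- Proportion near 50% in all 40: 1.96·√(0.25/40) = 0.155, about ±15 percentage points.
- Two-group standardised difference of about 0.5: 1.96·√(2/10 + 0.5²/40) = 0.89, about ±0.89 SD.

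**The case against.** The strongest reply is that the section does not claim outright that this trial has 80% power. It paraphrases a recommendation about pilot size, and the authors may have meant the power of the main trial that the pilot would help to plan. The reasons given for the lower end of the range also include participant burden and the feasibility objective, and these stand without the power clause. No significance-based decision rule is stated, and section 2.9 limits the comparisons to informing a later sample size. All of this stands. It limits the point to a wording error, but it does not make the sentence correct: the future-trial meaning is not in the text, and the cited source is not at hand to confirm it.

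Some stronger readings are not supported:
- **The trial is too small.** Low power for efficacy is not a design fault when feasibility is primary.
- **No two-group comparison of 10 to 20 per group could reach 80%.** This is too absolute. At 20 per group and d = 0.5, a baseline-adjusted test reaches about 83% to 94% if the correlation is 0.85 to 0.9, a high and assumed value. It does not rescue 10 per group, nor d = 0.2.
- **Choosing 10 rather than 20 presumes a particular phase III effect size.** Nothing in the article maps either number to an effect.
- **Stratified blocks will leave groups short of 10.** The text promises only a target of, or up to, 10 per group, and block sizes and the stratum mix are not given.

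**Conclusion.** The concern holds as a misstatement in section 2.8. The section attaches 80% power at 0.2 or 0.5 SD to groups whose unadjusted power is 7.1% and 18.5% at 10 per group and 9.5% and 33.8% at 20. The sizes needed for 80% exceed the planned 10 per group by factors of about 39 (394/10) and 6 (64/10).

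The figures rest on a two-group comparison of means with equal groups, a common SD and a two-sided 5% test. Baseline adjustment at 10 per group, under assumed correlations of 0.5 to 0.9, narrows the gap but does not close it. A reader might infer that the trial's conclusions depend on the false figure. The document does not support that, because the primary objective is feasibility and no decision turns on a significance test.

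**What to change.** In section 2.8:

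1. Delete the clause giving 80% power for effects of 0.2 or 0.5. Alternatively, if the cited source confirms it, state that the figure refers to the future main trial and not to this study.
2. Add that the between-group comparisons planned in section 2.9 are not powered at 10 per group and that their estimates will be imprecise.
3. Rest the choice of 10 per group on participant burden, feasibility and the precision it gives, quoting the three half-widths from Step 4 with the assumptions behind them.

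This is a change of wording only. It adds no participants and alters no endpoint or procedure. The one downside is that the stated property of the sample size becomes less favourable than the one now printed.

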### Data analysis plan

2.9

Data will be reported according to the CONSORT 2010 statement, extension for pilot and feasibility trials [46]. The research psychologist will perform the scoring cognitive tests and questionnaires scores and collation/tabulation of other endpoints prior to unblinded group analysis. Quantitative data will be analysed using SPSS version 24.0 [47]. We will provide descriptive statistics regarding the characteristics of the participants. Rates of consenting participants, recruitment, intervention completion, acceptability, tolerability, and adverse events will be reported by group on an intention-to-treat analysis (excluding participants who withdrew from the trial before the first iTBS administration).

Quantitative analysis will be used to evaluate the change in cognition, mood, and fatigue using the cognitive assessment and questionnaires. Where appropriate, parametric or non-parametric statistics will be used to estimate effect sizes and perform between-group comparisons to inform power and sample size calculations for a potential future phase III trial.

Qualitative data (post-intervention interviews) will be analysed using framework analysis [48–51]. These will be audio-recorded and transcribed verbatim by the research psychologist. The interview transcripts will be mapped onto a predefined framework. An analytical framework will be developed according to the interview schedule which will map onto the aims of the qualitative study. The researcher will read the transcripts to get familiar with the content of the interview. Subsequent analysis will be conducted on NVivo software [52]. This process will follow Gale et al.’s guide to framework analysis [48]. Following the initial coding of the first transcript, two researchers will meet to discuss the codes and to check whether the coding is consistent and comprehensive. Disagreements will be resolved through discussion together or with a third member of the study team to prevent bias. Once all the coding is completed, the researcher will enter these data onto the framework matrix and determine the fit of the data to this matrix. Any new data that does not fit the matrix will be considered again to see whether a new thematic structure is needed to include such data.

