### Intervention

2.5

Depending on the group, participants will receive iTBS (or sham) intervention 4 times per week for 1, 2, or 4 weeks. Each intervention session will last around 30 min, including 20 min of iTBS. The iTBS (or sham) sessions will be delivered by two TMS operators that completed 15 h of training to deliver TMS. The sessions will be conducted in a private and quiet room located at the Clinical Research Facility of Nottingham University Hospitals. The first intervention session will be scheduled for weeks 2, 4, or 5 depending on the group. We designed this study to have, for all participants regardless of group allocation, a 5-week standardised gap between baseline assessment on week 1, administrated before any iTBS session and the EOI assessments on week 5, administrated immediately after the last iTBS session.

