#### Baseline assessments and MRI scan

2.6.3

All participants regardless of group allocation will complete the following procedures at baseline assessment in week 1.

Participants will undergo in-person baseline cognitive and mood assessment that includes:The Brief International Cognitive Assessment for MS (BICAMS): The BICAMS was developed by an international panel to support a cognitive assessment that is brief and universal, to include tests of mental processing speed and memory. It was developed to be optimised for small centres where staff may not have formal neuropsychological training [32]. Tests included are:
The SDMT, assessing attention, working memory, and visual/spatial information processing speed [33].The California Verbal Learning Test-II, assessing verbal memory recall [34].The Brief Visuospatial Memory Test Revised, assessing visual memory [35].
Digit Span (from WAIS-IV): this test comprises two conditions, namely Digit Span Forwards (DSF) and Backwards (DSB). DSF assesses attention, encoding, and auditory processing capacity while DSB assesses working memory and executive function [36].Patient Health Questionnaire (PHQ-9) is a module of the PHQ for recording severity of depressive symptoms [26] and has been validated in primary care populations [37,38].Generalised Anxiety Disorder (GAD-7) is a brief scale to screen for generalised anxiety disorder [39].The Perceived Deficits Questionnaire (PDQ) assesses subjective cognitive dysfunction in people with MS [40]. The PDQ includes four subscales (attention/concentration, retrospective memory, prospective memory, and planning/organization).The Modified Fatigue Impact Scale (MFIS) is a self-report questionnaire exploring the effects of fatigue across physical, cognitive, and psychosocial modalities. It is a modified form of the Fatigue Impact Scale [41] and was developed following interviews with people with MS who discussed how fatigue had impacted their daily lives.The Edinburgh Handedness Inventory (EHI) assesses whether participants favour their left or right hand to inform the MRI analysis.

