#### Intervention visits

2.6.4

Two working days before the participants’ first visit, staff delivering the iTBS (or sham) intervention will ask participants if anything has changed since they were assessed which may impact their cognitive abilities, such as infection or MS relapse. If they have MS relapse or active/recent infection, they will be withdrawn from the study.

The first iTBS (active or sham) session will begin with the estimation of the RMT as detected using electromyography (EMG) to record a motor response in the contralateral abductor pollicis brevis. This is achieved by administration of single pulses of TMS to the scalp over the approximate location of the primary hand motor area of the left hemisphere, identified using the StimGuide neuronavigation system to locate the C3 position on the scalp. Slight adjustments to the position of the coil and the angle relative to the scalp surface are made by the operator to optimise stimulation of the primary hand motor area. The TMS operator delivers single TMS pulses with varying intensities guided by the adaptive Parameter Estimation by Sequential Testing [42] to estimate the participant’s RMT, defined as the minimum TMS intensity sufficient to produce a >50 μV motor‐evoked potential recoded by EMG in at least 50% of trials [43].

The localisation of the left DLPFC target will be identified using a similar target-identification methodology to previous work [23,44], using effective connectivity of the left caudate to identify the maximally connected locus in the left DLFPC.

The participant then receives the intervention according to group allocation as described above in the ‘Intervention’ section.

Following each administration, the participant is asked to report any sensations they may have experienced.

In case of missed appointments, the research team will work with the participant to reschedule the appointment, providing that participants do not have more than four consecutive days without intervention (including weekends) and that the total afforded extra time does not exceed 50% of the initial intervention schedule.

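### The set called intention-to-treat drops randomised people who leave before session 1, over windows of about 1, 3 or 4 weeks by schedule, so completion and retention rates can be overstated unequally

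*Protocol article*

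**What the plan says.** All references are to the Protocol article.

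- **Analysis set (2.9).** The set is described as an "intention-to-treat analysis (excluding participants who withdrew from the trial before the first iTBS administration". The plan applies it to this list of results: "Rates of consenting participants, recruitment, intervention completion, acceptability, tolerability, and adverse events will be reported by group".
- **Randomisation (2.4).** "Participants will be randomised after completing the consent form".
- **Baseline (2.6.3).** "All participants regardless of group allocation will complete the following procedures at baseline assessment in week 1".
- **Start of treatment (2.4 and 2.5).** The interval from baseline to end of intervention is fixed to protect the assessor's blinding, "requiring commencement of the iTBS intervention to be staggered per group as per Figure 2". Accordingly, "The first intervention session will be scheduled for weeks 2, 4, or 5 depending on the group", with "EOI assessments on week 5, administrated immediately after the last iTBS session".
- **Check two working days before the first visit (2.6.4).** "If they have MS relapse or active/recent infection, they will be withdrawn from the study".
- **What the groups are for (2.1).** Allocation is meant to let the feasibility and acceptability of the 1-, 2- and 4-week schedules be compared. Table 1 lists completion of the visit schedule among the primary endpoints, as a count.

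**The concern.** An intention-to-treat set keeps everyone randomised in the group to which they were allocated. This set removes people after allocation, so the label and the definition disagree.

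The exclusion would matter less if the gap between randomisation and treatment were the same in every arm. Here it differs by design. A relapse in week 3 comes before the first session in groups 1, 2 and 4. If it is found at the pre-first-visit check, the person is withdrawn and leaves the denominator. In group 3 the same relapse comes after the first session, and the person stays in the set whatever follows. Membership of the set therefore depends on allocation.

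A participant who consents, is randomised and leaves before treatment is a feasibility failure. The planned rates for completion and retention would not count that failure, and those rates are meant to inform the choice of schedule for a phase III trial.

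**Working it through.** **1. Waits.** Inputs: durations of 1, 2, 4 and 2 weeks for groups 1 to 4 (2.2), baseline in week 1 (2.6.3), last session in week 5 (2.5).

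Start week = 5 − duration + 1. Wait = start week − 1.

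| Group | Duration (weeks) | Start week | Wait (weeks) |
|---|---|---|---|
| 1 | 1 | 5 | 4 |
| 2 (real) and 4 (sham) | 2 | 4 | 3 |
| 3 | 4 | 2 | 1 |

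This reproduces the start weeks 2, 4 and 5 in section 2.5. The interval from consent to baseline is not stated, Figure 2 is not shown, and section 2.5 calls week 1 to week 5 a 5-week gap. Each wait may therefore shift by up to about a week, but the differences between groups do not change.

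**2. Effect of single exclusions, 10 per arm.** If 8 of 10 randomised complete, the all-randomised rate is 80%. With one of the other two lost before session 1, the planned set gives 8/9 = 88.9%. With both lost, it gives 8/8 = 100%.

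**3. Expected overstatement.** The documents give no pre-session loss rate. Assume a weekly loss probability h, equal in all arms, and 80% completion among starters. The planned set then reports 80% in every arm. The all-randomised rate is 0.80 × (1 − h)^wait.

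| h per week | Group 3 | Groups 2 and 4 | Group 1 |
|---|---|---|---|
| 0% | 80.0% | 80.0% | 80.0% |
| 1% | 79.2% | 77.6% | 76.8% |
| 2% | 78.4% | 75.3% | 73.8% |
| 5% | 76.0% | 68.6% | 65.2% |

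Over h = 1–5%, the overstatement is 0.8–4.0 points in group 3, 2.4–11.4 in groups 2 and 4, and 3.2–14.8 in group 1. The chance of at least one exclusion among 10, 1 − (1 − h)^(10 × wait), at h = 2% is 18%, 45% and 55% respectively.

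**4. A different assumption.** Suppose instead that the same weekly loss runs through both wait and treatment, and is the only reason for not completing. Wait plus duration is 5 weeks in every arm (1+4, 3+2, 4+1), so the all-randomised rate is (1 − h)^5 throughout: at h = 5%, 0.95^5 = 77.4%. The planned set gives (1 − h)^duration: 95.0% in group 1, 90.3% in groups 2 and 4, and 81.5% in group 3. That is a gap of 13.5 points between the shortest and longest schedules, produced only by the exclusion rule.

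**The case against.** The strongest reply has five parts.

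- **No loss is documented.** Correct: the overstatement is conditional, and it is zero if nobody leaves before session 1.
- **Most primary endpoints are untouched.** This largely stands. The completion endpoint in Table 1 is a count, which the exclusion does not change. Eligibility and consent have pre-randomisation denominators in Table 1. A treated set suits tolerability and adverse events. The experience questionnaire is completed at end of intervention (2.6.5), so early leavers would normally have no acceptability rating to include. What remains is the rate of completion and retention. The listing of consent and recruitment among rates reported by group is loose wording, since both come before allocation.
- **Early leavers are not lost from the evidence.** They are invited to exit interviews (2.6.7), and reporting follows the CONSORT pilot extension (2.9). This describes them but does not return them to the stated denominator.
- **An all-randomised rate can mislead too.** In step 3, group 1 looks worst only because it waits longest for blinding reasons. This is fair, and it is why completion among starters is worth showing as well. The all-randomised set still observes every arm over the same span from baseline to week 5.
- **Direction.** Longer waits exclude more people from group 1. A participant put off by 16 visits would be excluded from group 3, although eligibility already requires being able to attend for 4 weeks (2.3.1). The net direction cannot be fixed from the documents.

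A reader might infer that all primary feasibility rates are inflated, by a different amount in every arm, or that the comparison of schedules is biased by construction. The documents do not support that. There are three levels of wait, not four; the real-versus-sham pair (groups 2 and 4) has equal windows; and both the amount and the direction depend on losses that are not reported.

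**Conclusion.** The point holds for completion and retention rates. The set is mislabelled: it is a modified set with a post-randomisation exclusion, and the window for that exclusion is about 1, 3 or 4 weeks depending on schedule. If pre-session losses occur, these rates are overstated, and the amount can differ between the schedules under comparison. With 10 per arm, one excluded person is enough to move 80% to 89%. The 0.8–14.8 point range rests on assumed weekly losses of 1–5%, equal across arms, with 80% completion among starters; none of these is a figure from the trial. The text is wrong as written and should be corrected before the analysis.

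**What to change.** Amend section 2.9 as follows.

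1. For completion and retention, use all randomised participants, in their allocated group, as the denominator.
2. Report withdrawals before the first session by group, with the reason and the time waited.
3. Keep the set with at least one session for tolerability and adverse events, name it as a treated (modified) set, and show completion among starters as a supplementary figure.
4. Report acceptability ratings among respondents, with the number of randomised participants not rated in each group.
5. Report eligibility, consent and recruitment once, over all people screened or eligible, not by group.

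The cost is one paragraph of analysis wording and slightly less favourable completion figures. No new data are needed beyond recording the reason and date of each early withdrawal. The randomisation step need not move: section 2.12 reports 24 already recruited, so moving it now would mix two randomisation time points, and the denominator can be corrected without it.

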#### Secondary objectives

2.2.2

Secondary objectives are to:– Measure changes in cognitive assessment scores by group between baseline and EOI assessments (standardised interval of 5 weeks apart), to allow comparison of effect sizes between groups.– Measure changes in cognitive assessment scores by group between EOI and 8-week follow-up assessments, to allow comparison of effect sizes between groups.– Measure changes in participant-reported effects on cognition by group between baseline, EOI, and 8-week follow-up assessments, to allow the comparison of effect sizes between groups.– Explore (at the follow-up interview) participant views on meaningful change in cognition in relation to the demands of trial participation.– Measure changes in scores for anxiety, depression, and fatigue before and after intervention, to allow comparison of effect sizes between groups.– Measure changes in the effective connectivity between left DLPFC and left caudate nucleus, to allow correlation with changes in cognition.

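### Groups are to be compared on change from baseline, with no commitment to adjust for the baseline score; ANCOVA on the follow-up score would be more precise at almost no cost

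*Protocol article*

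**What the plan says.** The secondary objectives (section 2.2.2) are framed as change by group, for example "Measure changes in cognitive assessment scores by group between baseline and EOI assessments". The same framing covers the interval from end of intervention (EOI) to 8 weeks, self-reported cognition, and mood and fatigue, with comparison of effect sizes between groups as the stated purpose.

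The data analysis plan (section 2.9) repeats it: "Quantitative analysis will be used to evaluate the change in cognition, mood, and fatigue using the cognitive assessment and questionnaires". On method it says only that, where appropriate, "parametric or non-parametric statistics will be used to estimate effect sizes and perform between-group comparisons", in order to inform the power and sample size of a possible phase III trial. It names no model and no covariate, and it excludes none.

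Randomisation (section 2.4) is blocked and "stratified on: age group (≤40), gender (man or woman), and MS type (relapsing-remitting MS or secondary progressive or primary progressive MS". No baseline cognitive score is among these factors. On size, section 2.8 says "We aim to randomise up to 40 participants (up to 10 participants per group").

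**The concern.** The test is left open but the outcome scale is not: change between visits is what the groups are compared on. If that is carried out as a plain comparison of change scores, two things follow.

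First, precision is lost. The change score subtracts the whole baseline value, while the best linear prediction of follow-up from baseline uses a slope of r (equal variances). The excess subtraction adds noise.

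Second, chance baseline differences are not removed but partly reversed. A group that happens to start higher will tend to look worse on change, even with no treatment effect. In groups of about 10 such differences are common, and randomisation does not control them directly because baseline cognition is not a stratification factor.

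The stake is modest but specific. These effect sizes are meant to feed the design of a phase III trial, so avoidable noise in them passes into that planning.

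**Working it through.** **Inputs from the article.** Four groups, up to 10 each, so N = 4 × 10 = 40 (section 2.8). Outcome scale: change between visits (sections 2.2.2 and 2.9). Stratification factors: age group, gender, MS type (section 2.4). The article gives no SD, no correlation and no precision figure for these comparisons, so there is no stated result to reproduce.

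**Assumptions.** Equal SD at baseline and follow-up, set to 1. Correlation r between them from 0.5 to 0.9. Full recruitment of 10 per group.

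**1. How large a chance baseline imbalance is likely?** The SD of the difference between two group means is √(2/10) = 0.447 SD.
- Above 0.5 SD in either direction: 0.5/0.447 = 1.118, two-sided normal probability about 26%.
- Above 0.2 SD: 0.2/0.447 = 0.447, probability about 65%.

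The sample size section labels 0.2 and 0.5 as small and medium effects, so chance imbalances of that order are routine here.

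**2. What does a change score do with an imbalance D?** With no treatment effect, the expected follow-up difference given D is rD. The expected difference in change is rD − D = −(1 − r)D. With D = 0.5 SD:
- r = 0.5: −0.25 SD
- r = 0.8: −0.10 SD

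**3. Variance of the group difference.**
- Change: proportional to 2(1 − r).
- ANCOVA on follow-up with baseline as covariate: proportional to 1 − r².
- Ratio: (1 − r²)/[2(1 − r)] = (1 + r)/2.

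**4. Cost of estimating covariates.** With k covariate degrees of freedom and g = 4 groups, multiply by 1 + k/(N − g − k − 1). Baseline only (k = 1): 1 + 1/34 = 1.029. Baseline plus three two-level factors (k = 4): 1 + 4/31 = 1.129, taking the factors as not prognostic.

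| Assumed r | (1 + r)/2 | Baseline only | Baseline + three factors, not prognostic |
|---|---|---|---|
| 0.5 | 0.75 | 0.77 | 0.85 |
| 0.7 | 0.85 | 0.88 | 0.96 |
| 0.8 | 0.90 | 0.93 | 1.02 |
| 0.9 | 0.95 | 0.98 | 1.07 |

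Baseline adjustment alone gains at every r shown. The larger model breaks even where (1 + r)/2 × 35/31 = 1, that is r = 62/35 − 1 = 0.77. Above that it is less precise than change unless the factors predict outcome.

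**5. Where might r lie?** Not stated. Entry requires an SDMT score of 55 or lower and excludes a PHQ-9 score of 15 or more (sections 2.3.1 and 2.3.2), and both instruments are also outcomes. Restricting the range generally lowers r, which favours adjustment, but by how much cannot be worked out from the article.

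**The case against.** The strongest reply is that this is a condensed article, that covariates for secondary outcomes are normally left to the full protocol or SAP, and that nothing quoted forbids adjustment. ANCOVA is a parametric method, so the wording permits it. Change from baseline is also unbiased over repeated randomisations. All of this stands, and it limits the point: the article cannot be said to have chosen an unadjusted analysis. What it does not answer is that change is named, repeatedly, as the quantity to be compared, and that a better scale is available from data already being collected.

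A reader might go further and infer three things that the document does not support.

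- That the comparisons ignore the baseline score and the randomisation factors. A change score uses the baseline, with slope fixed at 1, and the factors are neither included nor excluded.
- That 8 strata (12 if MS type has three levels) for 40 people leave group sizes too uneven for an unadjusted comparison. Exact balance is indeed not guaranteed, but the plan says up to 10 per group, ANCOVA would not repair unequal sizes, and they cost little: 8 against 12 gives 1/8 + 1/12 = 0.208 against 0.200, or 4% more variance.
- That adjusting for everything narrows every interval at no cost. The last column of the table shows that it need not.

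It is also fair that the primary objective is feasibility, acceptability and tolerability (section 2.2.1), and that no efficacy conclusion rests on these comparisons.

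**Conclusion.** The point holds in a limited form. The article sets change between visits as the basis of between-group comparison and does not commit to baseline adjustment. ANCOVA on the follow-up score would cut the variance by about 23% at r = 0.5, 12% at 0.7, 7% at 0.8 and 2% at 0.9, after paying for one degree of freedom. It would also remove the reversed share of a chance baseline imbalance, which exceeds 0.5 SD in about one pairwise comparison in four.

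These figures rest on an assumed r, equal variances and 10 per group. The variance ratios apply to change measured from baseline, not to change from EOI to 8 weeks. Adding age group, gender and MS type has no assured benefit and can cost precision at high r. Severity is low: the comparisons are secondary, serve planning, and may already be specified in a document not shown.

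**What to change.** In section 2.9, state that each between-group difference in cognition, mood and fatigue will be estimated on the EOI score and on the 8-week score by ANCOVA, with the corresponding baseline score as covariate. Report adjusted differences with 95% confidence intervals. Keep change scores, including EOI to 8 weeks, as descriptive summaries by group.

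Treat age group, gender and MS type as optional covariates and say in advance whether they will be used.

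The cost is a change of wording and one model degree of freedom. No data collection, visit or participant is affected. If the full protocol or SAP already specifies baseline adjustment, a sentence saying so is enough.
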